**Repeat treatment**

Repeat radioiodine ablation will be given using the same administered activity as in the first attempt to ablate the thyroid. However, patients who are diagnosed with either regional metastases (includes patients who have pathologic uptake outside of the thyroid bed that is not compatible with salivary gland uptake) or distant metastases will be treated with administered activity of 4.4 MBq (120 mCi). If metastatic disease is not present but three or more radioiodine treatments are required to complete thyroid ablation, the administered activity needs to be at least 3.7 MBq (100 mCi) when the third (or subsequent) attempts to ablate the thyroid are made.

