**Background**

Some normal thyroid tissue is virtually always left behind in the neck following thyroidectomy for differentiated thyroid cancer. This thyroid tissue may or may not contain cancer. Lymph nodes of the neck may also contain metastatic cancer cells that have not been removed at surgery. Radioiodine is therefore usually administered postoperatively to eradicate both normal thyroid tissue and any remaining cancerous tissue.

The activities of radioiodine administered vary markedly in different countries ranging from 1.1 GBq to 7.4 GBq (from 30 to 200 mCi). Such substantial variation in radioiodine activity administered is due to a lack of properly conducted studies in this field. Only three randomized studies have been published, but these studies appear to have methodological shortcomings (Roos et al. 1998). In a small randomized study reported by Johansen et al. 36 patients were treated with radioiodine activity of 1,073 MBq (29 mCi) and 27 patients with 3,700 MBq (100 mCi). Ablation turned out to be equally effective in both groups (58% vs. 52%, respectively), but drawing reliable conclusions from this study is difficult. In another study (Creutzig et al. 1987) radioiodine activities of 1.1 GBq (30 mCi) and 3.7 MBq (100 mCi) were compared in a cohort of 20 patients who did not have metastatic lymph nodes in the neck. No difference in outcome was detected, but the size of the study was again very small. The largest randomized study has been carried out by Bal et al. (1996). In this study the randomization procedure may not have been appropriate, because the patients´ ability to pay for hospital costs influenced randomization, and similarly the radioiodine activity available at the hospital at the time of study entry probably also affected randomization. One hundred and forty-nine patients took part in this trial, and the administered radioiodine activities were 1,110 MBq (30 mCi), 1,850 MBq (50 mCi), 3,700 MBq (100 mCi) or 5,550 MBq (150 mCi). Thyroid ablation was successful in 63% if the cases treated with 1,110 MBq and in 77% of those who received administered activity of 5,550 MBq.

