**Aims of the study**

The aims of the study are the following:

1. To compare efficacy of two administered activities of radioactive iodine in terms of ablating the thyroid following thyroidectomy. The compared activities will be 1,110 MBq (30 mCi; used e.g. in the United States of America and in France) and 3,700 MBq (100 mCi, the activity usually administered e.g. in Finland).

2. To compare subjective and objective adverse effects between the two groups; and to compare costs related to these treatments (assessed based on the number of days spent in a hospital isolation unit).

3. To evaluate factors that might be predictive for successful ablation, such as the number of metastatic cervical lymph nodes, and the measured absorbed dose at the thyroid bed.

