**Treatment allocation groups**

The study participants will be randomly allocated to receive either 1,110 MBq (30 mCi) or 3,700 MBq (100 mCi) of radioactive iodine following thyroidectomy.

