**Study procedures**

Eligibility to the study will be assessed three to four weeks after surgery by a physician. Concomitant diseases, symptoms and physical status will be assessed. The potential study participants will be informed about the study both orally and in writing. Random allocation between the radioiodine activities [1.1 GBq (30mCi) or 3.7 GBq (100mCi)] may occur after the patient has signed an informed consent.

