**Radioiodine administration schedule (please see also institutional guidelines for radioiodine administration)**

**Study Day: Procedure:**

Day -5 (Wednesday) 4 to 5 weeks from surgery The following blood tests will be carried out: serum thyroglobulin, thyroid stimulating hormone, free tri- iodothyronine (T3); blood haemoglobin, white cell count, platelet count; serum Na, K, creatinine, aspartate amino transferase (AST). 7.4 MBq radioiodine is administered orally.

Day -4 (Thursday) Filling of baseline symptom/toxicity questionnaire. Neck radioiodine uptake measurement.

Day 0 (Monday) Radioiodine treatment (either 1,110 or 3,700 MBq, administered as a capsule orally); Geiger counts measured on the neck.

Day +1 and +2 (Tue/Wed) Body Geiger counts measured; discontinuation of isolation allowed when measured total body activity is <15 uSv.

Day +4 (Friday) SPECT and Geiger measurements; filling of adverse event questionnaire; whole body iodine scan

Day +11 (Friday) Neck CT.

Day +14 (Friday) A telephone call to the patient to inform about the results of the scans, filling of the adverse event questionnaire.

Day +90 Hospital visit; includes response evaluation by the physician, filling of the adverse event questionnaire and laboratory tests (serum thyroglobulin, thyroid stimulating hormone, free tri- iodothyronine (T3); blood haemoglobin, white cell count, platelet count; serum Na, K, creatinine, aspartate amino transferase).

**Note**: In case metastatic disease is diagnosed in the whole body iodine scan taken following administration of the ablative dose (this is rare), a supplementary activity of 70 mCi will be administered to the patients who were allocated to receive 1,100 mBq (30 mCi). Patients allocated to the higher activity group (3700 MBq, 100 mCi) will not receive a supplementary dose, but the patients will be evaluated, and repeat radioiodine treatment will be administered if clinically required at approximately 4 months after the date of administration of the first dose.

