**Treatment evaluation and study endpoints**

Radioiodine ablation will be evaluated from the following points of view: 1) success of ablation and how often radioiodine treatment needs to be repeated to complete ablation 2) change in the serum thyroglobulin levels 3) adverse events of treatment (as assessed with questionnaires and blood tests) 4) as times of disease-free survival and overall survival, and 5) duration of stay in a hospital isolation unit.

Radioiodine treatment is deemed unsuccessful and needs to be repeated whenever

1) abnormal uptake (compatible with presence of thyroid tissue or cancerous tissue) is present in a diagnostic whole body 131I scan carried out with 185 MBq (5 mCi) activity after a minimum of 4 months following radioiodine administration, and a after a minimum of 4-week interruption of thyroxin administration

2) detectable (1 ng/mL or higher) levels of thyroglobulin are present in the serum 4 months or later from the date of administration; includes serum thyroglobulin levels measured under thyroid stimulating hormone (TSH) stimulation (achieved by interruption of thyroxine administration for a minimum of 4 weeks).

3) or palpable neck metastases are detected.

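### The two fixed repeat-treatment activities are printed in MBq where GBq is meant, a factor of about 1,000 below the mCi values beside them

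*Protocol*

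**What the plan says.** The Repeat treatment section of the Protocol makes the first activity the default for a repeat ablation, then sets two fixed activities that override it:

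- Patients with regional or distant metastases "will be treated with administered activity of 4.4 MBq (120 mCi").
- Without metastatic disease, from the third attempt onward, "the administered activity needs to be at least 3.7 MBq (100 mCi").

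Other sections pair becquerels with millicuries for the same treatment:

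- Aims of the study: the higher activity is "3,700 MBq (100 mCi, the activity usually administered e.g. in Finland").
- Treatment allocation groups: "either 1,110 MBq (30 mCi) or 3,700 MBq (100 mCi) of radioactive iodine".
- Study procedures: "Random allocation between the radioiodine activities [1.1 GBq (30mCi) or 3.7 GBq (100mCi")].
- Treatment evaluation and study endpoints: the diagnostic scan is "carried out with 185 MBq (5 mCi) activity".
- Background: activities in use are described as "ranging from 1.1 GBq to 7.4 GBq (from 30 to 200 mCi").

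Two other places carry unit slips. The note at the end of the radioiodine administration schedule gives the low arm as 1,100 mBq (30 mCi). The Background gives 3.7 MBq (100 mCi) when describing one small cited study.

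**The concern.** 100 mCi appears as 3,700 MBq in the aims and the allocation section, as 3.7 GBq in the study procedures, and as 3.7 MBq under Repeat treatment. The last cannot be right if the others are. The 120 mCi figure has the same fault.

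This text orders a treatment; it is not background. MBq is also a working unit in this Protocol: the Day 0 entry reads "Radioiodine treatment (either 1,110 or 3,700 MBq, administered as a capsule orally"), with no mCi figure. Taken alone, the two units would give opposite instructions for a low-arm patient at a third attempt. The 1,110 MBq default already exceeds a floor of 3.7 MBq, so nothing would change. Against a floor of 100 mCi, 30 mCi falls short and the activity must be raised. A dosing instruction should state one quantity.

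**Working it through.** **Conversion implied by the Protocol's own pairs** (MBq divided by mCi):

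| Section | Pair | MBq per mCi |
|---|---|---|
| Aims; Treatment allocation groups | 1,110 MBq / 30 mCi | 37.0 |
| Aims; Treatment allocation groups | 3,700 MBq / 100 mCi | 37.0 |
| Study procedures | 3.7 GBq / 100 mCi | 37.0 |
| Study procedures | 1.1 GBq / 30 mCi | 36.7 (1.1 is 1.11 rounded) |
| Treatment evaluation and study endpoints | 185 MBq / 5 mCi | 37.0 |
| Background, range in use | 7.4 GBq / 200 mCi | 37.0 |

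The factor is therefore 37 MBq per mCi.

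**The Repeat treatment pairs as printed:**

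- 4.4 / 120 = 0.0367 MBq per mCi
- 3.7 / 100 = 0.037 MBq per mCi

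**What the mCi values require** (MBq = mCi × 37):

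- 120 × 37 = 4,440 MBq; 4,440 / 4.4 = 1,009
- 100 × 37 = 3,700 MBq; 3,700 / 3.7 = 1,000

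**What the printed MBq values would be in mCi:**

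- 4.4 / 37 = 0.119 mCi
- 3.7 / 37 = 0.10 mCi

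**Which number is wrong.** Both printed becquerel values lie below the 7.4 MBq uptake tracer of Day -5 (4.4 / 7.4 = 0.59; 3.7 / 7.4 = 0.50) and far below the 185 MBq diagnostic scan. Neither can be a therapeutic activity. The mCi values are on the scale of the randomised activities.

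**Check of the correction.** With GBq in place of MBq, 4,400 / 120 = 36.7 and 3,700 / 100 = 37.0. Both pairs then agree, the first to rounding.

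**The other two slips.** In the schedule note, 30 × 37 = 1,110 MBq. The printed unit, read literally, is the millibecquerel, and 1,100 is a rounding of 1,110. In the Background, the 3.7 MBq / 100 mCi pair has the same ratio of 0.037 as the second Repeat treatment pair. So it would be wrong to say that every pair outside Repeat treatment gives 37.

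**The case against.** The strongest reply is that the slip corrects itself. Each wrong figure stands next to the right mCi value, the 100 mCi pair is printed correctly in three other sections, and the Repeat treatment section opens by tying the default to the first activity. A clinician reading it has the intended activity in view. Success in the power calculation is defined on one treatment, and these rules apply only after that. This all stands, and it is why the point ranks as minor. It does not make the text correct.

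A reader might go further than the Protocol allows in three ways:

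- **That patients would be underdosed 1,000-fold, or that low-arm patients would never be escalated.** This needs the MBq figures to be read without their mCi values, and the Protocol never prints them so. The opposite instructions described above show why the text needs correcting; they do not predict what would happen.
- **That the trial's main comparison is compromised.** The randomised activities are stated consistently apart from the prefix slip in the schedule note, and the sample size takes no input from the repeat-treatment rules.
- **That the schedule's 70 mCi supplement confirms the conversion,** since 30 + 70 = 100 mCi. The supplement is given only in mCi, so it cannot test an MBq-to-mCi factor, and the Protocol does not say that it is meant to reach 100 mCi.

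A fault in reading the PDF is an unlikely explanation: GBq is read correctly in the Background and the study procedures, and the same wrong prefix appears in both Repeat treatment pairs and again in the Background.

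**Conclusion.** The point holds, at minor severity and with high confidence. Both fixed repeat-treatment activities contradict the mCi values beside them by a factor of about 1,000 (1,009 and 1,000), and GBq is the right unit. The conclusion rests only on the Protocol's own pairs and on taking the mCi figures as intended, which the tracer and diagnostic-scan activities support.

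The effect is confined to the wording of the repeat-treatment rules and the schedule note. Actual misdosing is unlikely. The randomised comparison and the planned 160 patients are unaffected. The Protocol does not report whether anyone has yet had a repeat treatment, so nothing can be said about a number of patients affected or about data already collected.

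**What to change.** In one amendment:

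1. Repeat treatment, metastatic disease: 4.4 GBq (120 mCi).
2. Repeat treatment, third or later attempt: at least 3.7 GBq (100 mCi).
3. Radioiodine administration schedule, supplementary-dose note: replace 1,100 mBq with 1,110 MBq (30 mCi).

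The Background figure for the cited study (3.7 MBq for 100 mCi) can be changed to GBq at the same time. It is descriptive and directs no treatment.

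The cost is three unit corrections in operative text and one optional correction in the Background. No activity, endpoint, analysis or sample size changes.

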**Study power**

We estimate that one radioiodine treatment is successful in 40% of the patients allocated to receive the smaller administered dose (1,100 MBq) and in 60% of the patients allocated to the higher activity (3,700 MBq) group. Using a power (1-) 80%,  0.05 and a one-sided log-rank test, 80 patients need to be recruited to each one of the study arms.

Estimation of patient accrual rate: The number of patients diagnosed with either papillary or follicular thyroid cancer at the Department of Oncology, Helsinki University Central Hospital, and treated with radioiodine after thyroidectomy ranges from 50 to 60 per annum. We estimate that 40 to 50 of these patients may fulfil the inclusion criteria of the study. The duration of the study accrual is estimated to be 3 to 4 years provided that a total of 160 patients are entered to the study.

An interim safety analysis: The study will be discontinued if a difference of 50% or greater will be detected in the proportions of patients whose thyroid is successfully ablated (with no need for retreatment) when one half or the study participants (80 patients) have been treated in the study (p is <0.01).

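### The sample-size statement names a log-rank test for a yes/no endpoint; a comparison of two success proportions should be named instead, and 80 per arm then stands

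*Protocol*

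**What the plan says.** The Protocol, section Study power, assumes that "one radioiodine treatment is successful in 40% of the patients allocated to receive the smaller administered dose" and "in 60% of the patients allocated to the higher activity (3,700 MBq) group". With 80% power and a level of 0.05 it then states, on the basis of "a one-sided log-rank test, 80 patients need to be recruited to each one of the study arms", a total of 160. The interim rule in the same section compares the proportions ablated without retreatment.

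The section Treatment evaluation and study endpoints defines failure by findings: abnormal uptake on a diagnostic scan, serum thyroglobulin of 1 ng/mL or higher, or palpable neck metastases. The scan is done "after a minimum of 4 months following radioiodine administration", and the thyroglobulin criterion likewise applies from 4 months on. Neither has a latest date. The same section lists disease-free and overall survival, but the power statement gives no rates for them. The section Randomisation stratifies by cervical lymph node (N) status.

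The log-rank test appears only in the sample-size sentence. No other test is named anywhere in the Protocol.

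**The concern.** A log-rank test compares times to an event. The quantity that the trial is sized on is whether one treatment worked, and for nearly every patient that is learned on the day of the evaluation scan and thyroglobulin test. If this outcome is given a time at all, the obvious candidate is the assessment date, which reflects scheduling and not ablation.

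An analyst who follows the sample-size sentence must decide what counts as the event, what time to attach to it, and when patients without the event leave the risk set. The Protocol settles none of these. One ordinary choice, censoring each success at its own last assessment, makes the result depend on when patients were scanned. At stake are the power of the main comparison and its protection against a false positive.

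**Working it through.** **Inputs from the Protocol (Study power):** success 0.40 (low activity) and 0.60 (high activity), one-sided level 0.05, power 80%, 80 per arm. The normal quantiles are 1.645 and 0.842.

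**1. Reproducing 80 per arm**

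- Two proportions, pooled variance: n = [1.645 × √(2 × 0.5 × 0.5) + 0.842 × √(0.24 + 0.24)]² / 0.20² = (1.163 + 0.583)² / 0.04 = 76.2, so 77 per arm.
- Power at 80 per arm: Φ[(0.20 × √80 − 1.163) / 0.693] = Φ(0.903) = 81.7%. Exact enumeration of the same z-test gives 81.3%.
- Log-rank, failure as the event: hazard ratio = ln 0.40 / ln 0.60 = 1.79. Freedman: (1.645 + 0.842)² × [(1.79 + 1)/(1.79 − 1)]² = 76.6, so 77 events. With an average event fraction of 0.5 this is 154 patients, 77 per arm. Schoenfeld gives 73 events, 73 per arm.

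Either route leads to a figure slightly below 80, so the stated number is sound for its own inputs.

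**2. Why the coding of time matters**

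Under 40% against 60%, expected failures are 80 × 0.60 = 48 and 80 × 0.40 = 32, a total of 80. Half the total is 40, so observed minus expected is 8 in either arm.

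- *All outcomes at one time.* There is one risk set of 160, and the log-rank variance is 80 × 0.5 × 0.5 × 80/159 = 10.06. Then z = 8/√10.06 = 2.52, and power is about Φ(2.52 − 1.645) = 81%. The log-rank test has become the comparison of two proportions.
- *Successes censored at their own scan, scan dates well spread and equal in both arms.* Most risk sets contain one event and remain about half and half, so the variance is about 80 × 0.25 = 20. Then z = 8/√20 = 1.79, and power is about Φ(1.79 − 1.645) = 56%.

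**3. Simulation**

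Settings: 80 per arm, one-sided 0.05, failure as the event, 1,500 to 2,000 replicates per setting (figures can move by one to three points between runs). The scan windows and the one-week shift are assumptions; the Protocol gives neither. Power is for 40% against 60%; the false-positive rate is for no true difference (50% in each arm).

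| Assumed scan weeks | Successes censored at own scan: power | False positives, low-activity arm one week earlier | Power, low-activity arm one week later | Successes kept at risk: power |
|---|---|---|---|---|
| 17-26 | 61% | 49% | 8% | 80% |
| 17-35 | 60% | 24% | 21% | 81% |
| 17-52 | 56% | 13% | 35% | 80% |

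With successes kept at risk, the one-week shift gives a false-positive rate of only 5-9%, and power of 73%, 75% and 78% when the low-activity arm is later. With all outcomes read at one common time, power is 79-83% and the false-positive rate is about 4-6%.

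**The case against.** The strongest reply is that the loss is not a consequence of the plan. The Protocol does not say that successes are censored at their scan date, the 4-month minimum applies to both arms alike, and nothing in it schedules the arms' evaluation scans differently. Under two other codings the log-rank test keeps close to 80% power. This stands. A reader might infer that the trial will compare scan dates, or that it cannot reach its stated power; the document supports neither.

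It can also be said that log-rank is named only in the sample-size sentence, that the interim rule already treats the outcome as a proportion, and that the final test may be set in a statistical analysis plan that is not shown. This stands in part. It is an inference that log-rank is the planned primary analysis, and leaving details to a later plan is no fault. But the test that the Protocol does name does not match the quantity it is sized on.

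Finally, log-rank would suit the listed survival endpoints, and one could construct a time to complete ablation over repeat treatments. The 40% and 60% are neither of these: they are success after a single treatment.

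**Conclusion.** The mismatch is plain from the text: a time-to-event test is attached to a yes/no result after one treatment, with no event time, no censoring rule and no latest assessment date. Harm to power and error control is possible, not certain. It requires that successes be censored at their own scan date and that scan dates vary (power about 56-61%). The inflated false-positive rate of about 13-49% also requires that the low-activity arm be scanned a week earlier on average. Under the other codings examined, with timing equal in both arms, power stays at 79-83%.

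The sample size is not in error. At one-sided 0.05 a comparison of proportions needs 77 per arm, and 80 give about 81-82% power. Those figures are for the unstratified test; the Protocol gives no success rates by N status from which to compute the stratified one.

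**What to change.** In the Protocol, section Study power, replace the log-rank test with a one-sided comparison of the two proportions successfully ablated by one treatment, stratified by N status, which is already the randomisation stratum. A Cochran-Mantel-Haenszel test would serve, reported with a risk difference and its confidence interval. Keep log-rank for disease-free and overall survival.

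The cost is one sentence, with no additional patients or data, and 80 per arm is unchanged. The test then no longer uses the order of scan dates or any censoring rule. The open upper limit on assessment time is a separate matter that this change does not close.
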